## Abstract

**Background:**

Poor ovarian response (POR), a manifestation of low ovarian reserve and ovarian aging, leads to a significant reduction in the pregnancy rate after in vitro fertilization-embryo transfer. Acupuncture has increasingly been used to improve the ovarian reserve. The purpose of this study will be to evaluate the effect of acupuncture on increasing the number of retrieved oocytes after controlled ovarian hyperstimulation in women with POR.

**Methods:**

This will be a multicenter randomized controlled trial. A total of 140 women with POR will be randomly assigned to receive acupuncture or nontreatment for 12 weeks before controlled ovarian hyperstimulation. The primary outcome will be the number of retrieved oocytes. The secondary outcomes will be antral follicle counts, serum levels of anti-Müllerian hormone, basal serum levels of follicle stimulating hormone, luteinizing hormone and estradiol levels, scores from the self-rating anxiety scale, fertilization rates, cleavage rates, available embryo rates, and high-quality embryo rates. The safety of acupuncture will also be assessed.

**Discussion:**

The results of this trial will help to determine the effectiveness of acupuncture in the treatment of POR. This may provide a new treatment option for patients with POR and their physicians.

**Trial registration:**

AMCTR-IPR-18000198. Registered on 10 August 2018.

## Background

Poor ovarian response (POR) indicates a reduction in follicular response to the controlled ovarian hyperstimulation (COH) during in vitro fertilization (IVF) cycles, and it results in a reduced number of retrieved oocytes [1]. It is believed that approximately 9–24% of women who undergo IVF show POR during COH [2]. Women with POR usually experience less follicular development in COH cycles, low blood estrogen levels, high doses of gonadotrophin, high cycle cancelation rates, decreased numbers of retrieved follicles, and low rates of clinical pregnancy [3]. Therefore, POR often leads to an unsatisfactory outcome in assisted reproductive technology (ART), which seriously affects physical and mental health as well as quality of life.

An individualized COH protocol designed according to the assessment of ovarian reserve is the key to success of POR treatment in the first and multiple cycles. Various protocols of ovarian stimulation, including gonadotrophin-releasing hormone (GnRH) agonist protocols [4], GnRH antagonist protocols [5], and some nontraditional protocols (microstimulation, natural cycles, luteal ovulation, etc.), have been proposed for optimizing ART outcomes; however, challenges remain for women with poor responses to COH. Many pretreatment modalities (including growth hormone, estrogen, dehydroepiandrosterone, and oral contraceptives) have been used prior to ovulation induction to increase the success rate for women undergoing ART [6–8], and yet evidence for the effectiveness of these pretreatments are limited [9].

Acupuncture, an important part of traditional Chinese medicine, has gained worldwide popularity for improving reproductive outcomes in women undergoing ART. Although high-quality research is still needed, several lines of evidence have shown that acupuncture is effective at increasing the number of retrieved oocytes [10], improving clinical pregnancy rate and live birth rate [11, 12], and relieving anxiety [13] in women who undergo in vitro fertilization-embryo transfer (IVF-ET). Low ovarian reserve often indicates a poor ovarian response in COH. Although acupuncture has not been studied for POR, its effectiveness in improving ovarian reserve for women with diminished ovarian reserve (DOR) or premature ovarian insufficiency (POI) has been reported. The results of our previous studies showed that acupuncture significantly lowered serum levels of follicle-stimulating hormone (FSH) and luteinizing hormone (LH), raised serum levels of anti-Müllerian hormone (AMH) and estradiol (E2), and increased antral follicle count (AFC) in patients with DOR [14, 15] or POI [16]. Acupuncture was found to regulate the menstrual cycle and to improve perimenopausal symptoms [14, 15].

Given its effect on the improvement of ovarian reserve and ART outcomes, acupuncture is expected to be a new choice for the treatment of POR. Furthermore, POR patients treated by transcutaneous electrical acupoint stimulation (TEAS), a noninvasive acupuncture-like therapy, showed significant improvement on basal serum sex hormones, AMH, the number of retrieved oocytes, and fertilization rate [17, 18], which indirectly indicated the effect of acupuncture for POR. Therefore, we aim to conduct a multicenter, randomized controlled trial (RCT) to evaluate the effectiveness of acupuncture on women with POR.

## Methods

### Study design

This will be an exploratory multicenter randomized controlled trial comparing acupuncture with nontreatment. A total of 140 women with POR will be recruited from the following 9 hospitals in China: Shanxi Provincial Hospital of Chinese Medicine, Shandong University Reproductive Hospital, Sun Yat-sen Memorial Hospital of the Sun Yat-sen University, Lanzhou University First Hospital, People’s Hospital of Henan Province, Huazhong University of Science and Technology Reproductive Medicine Center of Tongji Medical College, Shanghai Shuguang Hospital, Nanjing General Hospital of Nanjing Military Command, and Luoyang Women and Children Health Care Center. This protocol is in accordance with the principles of the Declaration of Helsinki. It was approved by the ethics committee of each participating hospital. Written informed consent will be obtained from patients prior to enrolment.

Eligible patients will be randomly assigned to receive acupuncture or nontreatment for 12 weeks, which will be followed by an IVF cycle. Outcomes will be assessed at baseline, after acupuncture or nontreatment intervention, and after the IVF cycle. The flowchart and study design schedule are presented in Fig. 1 and Table 1, respectively. This protocol has been registered at Acupuncture-Moxibustion Clinical Trial Registry (AMCTR-IPR-18000198).

**Fig. 1 Fig1:**
[figure not shown]
Trial flow chart

**Table 1 Tab1:** Study design schedule

Period	Screening	Baseline	Intervention	COH
Week (***W***)		***W***0	***W***12	***W***14
Informed consent	**×**			
Eligibility	**×**			
Demography and medical history	**×**			
AFC		**×**	**×**	
Serum level of AMH		**×**	**×**	
Basal serum levels of FSH, LH, and E2		**×**	**×**	
Score of SAS		**×**	**×**	
Number of retrieved oocytes				**×**
Number of fertilized oocytes				**×**
Number of cleavage				**×**
Number of available embryos				**×**
Number of high-quality embryos				**×**
AEs		**×**	**×**	**×**
Compliance		**×**	**×**	**×**

*AFC* antral follicle count, *AMH* anti-Müllerian hormone, *FSH* follicle-stimulating hormone, *LH* luteinizing hormone, *E2* estradiol, *SAS* self-rating anxiety scale, *AEs* adverse events

### Participants

We plan to recruit 140 women with POR from participating hospitals via poster, networking, or WeChat. The posters will be placed on bulletin boards or other assigned places in the hospitals. In each participating hospital, at least one staff member (usually a postgraduate or doctor) will specialize in patient recruitment. Their contact information and clinic for screening visit will be detailed described in the recruitment advertisement.

Participants will be included if they meet the following criteria: (1) diagnosis with POR according to the Bologna criteria published in 2011 by the European Society of Human Reproduction and Embryology [1]; (2) age < 40 years; (3) previous POR (≤ 3 oocytes retrieved in a conventional stimulation protocol); (4) an abnormal ovarian reserve test (i.e., AFC < 5–7 follicles or AMH < 0.5–1.1 ng/ml) or two episodes of POR after maximal stimulation; (5) suitability for GnRH antagonist protocol judged by physicians of reproductive medicine; and (6) voluntary participation and signing of the informed consent.

Participants will be excluded if they meet any of the following criteria: (1) history of ovarian surgery, radiotherapy or chemotherapy; (2) repeated miscarriages (including biochemical pregnancy) of more than 2 sessions; (3) repeated implantation failure (experienced at least 3 embryo transfer cycles, or failure to achieve clinical pregnancy after cumulatively transferring 10 good quality embryos); (4) uterine malformations (unicornate uterus, bicornuate uterus, uterus didelphys, or untreated uterus septus) or other untreated diseases that can damage the endometrial cavity such as adenomyosis, submucous myoma, intrauterine adhesions, and scarred uterus; (5) abnormal chromosomes in the patient or her partner (except chromosomal polymorphism); (6) untreated hydrosalpinx; (7) contraindications for pregnancy or ART; (8) untreated diseases that can negatively affect pregnancy such as high blood pressure, symptomatic heart disease, diabetes, liver or kidney disease, severe anemia, venous thrombosis, cerebral vascular diseases, and cancer; and (9) treatment with acupuncture or moxibustion treatment for POR in the previous 3 months.

### Randomization and masking

Block randomization stratified by center will be applied in this trial. Eligible participants will be randomly assigned to acupuncture or nontreatment groups in a 1:1 ratio. The scheme of randomization including any planned restriction (e.g., blocking) will be designed and archived by a statistician who will not be involved in the statistical work of this trial. The allocation sequence will be computer-generated. If a participant is eligible for the trial, the appointed researcher (acupuncturist or reproductive physician) in each center will apply for the random number and group assignment via a telephone- and internet-based central randomization system of the Clinical Evaluation Center of the China Academy of Chinese Medical Sciences. A strict view permission will be set for the central randomization system, which allows no one except the top system administrator to view its randomization scheme. In this study, outcome assessors and data analysts will be blinded to group allocation.

### Interventions

#### Acupuncture protocol

Patients in the acupuncture group will receive a 12-week acupuncture treatment regimen before COH. Acupuncture will be performed by registered acupuncturists with over 2 years of experience. Hwato brand disposable acupuncture needles (size 0.25 × 25 mm, size 0.25 × 40 mm, and size 0.30 × 75 mm) and SDZ-III electroacupuncture apparatuses (Suzhou Medical Appliance Factory, Suzhou, China) will be used.

The acupuncture protocol designed for this trial is based on our clinical practice for improving ovarian function for women with DOR [14]. It consists of two groups of acupoints: Group 1 (in supine position): GV20 (Baihui), GV24 (Shenting), GB13 (Benshen), CV12 (Zhongwan), ST25 (Tianshu), CV4 (Guanyuan), KI12 (Dahe), EX-CA1 (Zigong), SP6 (Sanyinjiao), KI3 (Taixi), LR3 (Taichong); and group 2 (in prone position): BL23 (Shenshu) and BL33 (Zhongliao). These two groups of acupoints will be used alternatively with group 1 as the initial treatment. All acupoints will be located according to the World Health Organization Standardized Acupuncture Points Location [19]. A needle depth of 10 to 20 mm will be applied for GV20, GV24, and GB13 with transverse insertion and for LR3 with oblique insertion to the direction of KI1 (Yongquan). BL33 will be needled with an oblique downward trajectory of approximately 60 to 70 mm into the third posterior sacral foramina. The remaining acupoints will be perpendicularly needled for approximately 30 to 40 mm. After insertion, small, equal manipulations of lifting, thrusting, or twirling will be performed on all needles (for GV20, GV24 and GB13, twirling only) to reach deqi, a composite of sensations (including soreness, numbness, distention, and heaviness) recognized as an essential component in achieving the acupuncture effect. In acupuncture with acupoints of group 2, paired electrodes from the electroacupuncture apparatus will be attached transversely to the needle handles at bilateral BL23 and BL33 with a dilatational wave and a current intensity that patients can tolerate (preferably with the skin around the acupoints shivering mildly without pain). Each acupuncture session will last for 20 min. Participants will receive 3 sessions of acupuncture per week (ideally every other day) for 12 consecutive weeks for a total of 36 sessions.

#### Nontreatment control

Participants in the control group will receive nontreatment for 12 weeks before COH.

#### COH regimen

Participant will start COH with a GnRH antagonist protocol on day 2 or 3 of the menstrual cycle after acupuncture or nontreatment period. GnRH antagonists are commonly used to prevent the premature LH surge that often occurs in poor responders [20, 21]. This induces pituitary suppression within a few hours without a flare-up effect, and the suppression is released immediately after their discontinuation [22]. Compared with GnRH agonist, GnRH antagonist protocol shows a shorter treatment time, a lower dosage of Gn, and a similar clinical pregnancy rate [5]. In this trial, individualized GnRH antagonist protocol will be administered by physicians of reproductive medicine in each center. Given that participants may become suitable for COH before they complete the 12-week acupuncture or nontreatment, an early termination of acupuncture or nontreatment aiming to seize the opportunity to initiate a COH cycle will be allowed on the condition that they complete at least the 4-week acupuncture treatment (12 sessions of acupuncture) or nontreatment period.

### Permitted and prohibited concomitant treatments

Participants will be discouraged from taking drugs that may interfere with the assessment of acupuncture effect, including Chinese herbs, Chinese patent medicine, sexual hormones, and contraceptives. If treatment not recommended in this trial has already been performed, relevant information should be recorded in patient’s case report form.

### Outcome measures

The primary outcome is the number of retrieved oocytes. The secondary outcomes include the assessment of ovarian reserve (AFC and serum levels of AMH, FSH, LH, and E2), other IVF outcomes (fertilization rate, cleavage rate, available embryo rate, and high-quality embryo rate), and the score of the self-rating anxiety scale (SAS). Ovarian reserve will be assessed at baseline and after acupuncture or nontreatment period. AFC (via transvaginal ultrasound) and serum levels of FSH, LH, and E2 are required to be measured on days 2 to 5 of the menstrual cycle. AMH can be measured on any day of the menstrual cycle. SAS is a self-rating scale for measuring the presence and severity of anxiety [23]. A validated Chinese version of SAS will be used [24]. It consists of 20 items rated on a 4-point Likert scale. When using the scale, participants will be asked to rate each item from 1 to 4 points according to how it applies to them within the past week. The standard score is the sum of the integer part of 1.25 times the raw score (the sum of the 20 items ranging from 20 to 80). The presence of anxiety symptoms is defined as an SAS standard score of greater than 50. A higher score indicates a more serious case of anxiety. SAS will be assessed at baseline and after acupuncture or nontreatment period.

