#### Statistical analysis

Statistical analysis will be performed by a statistician blinded to group assignments using SAS version 9.4 (SAS Institute Inc). All analyses will be based on the intention-to-treat principle. Missing data will be imputed using the multiple imputation method. Continuous data will be presented as the mean and standard deviation, or the median and interquartile range; categorical data will be presented as the number and percentage. Comparisons between groups will be analyzed using an independent *t*-test or Wilcoxon rank-sum test for continuous variables, and a chi-square test or Fisher exact test for categorical variables. All statistical tests will be two-sided, and *p* < 0.05 will be considered statistically significant.

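### The four embryology rates are ratios of post-randomization counts and do not exist for women with a zero denominator, so they cannot be the intention-to-treat comparisons promised for all analyses

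*Protocol article*

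**What the plan says.** Under Outcome measures, "The primary outcome is the number of retrieved oocytes", and the secondary outcomes include "other IVF outcomes (fertilization rate, cleavage rate, available embryo rate, and high-quality embryo rate"). The section names the rates without writing out their denominators.

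Table 1 (study design schedule) lists counts only in the COH column: oocytes retrieved, then "Number of fertilized oocytes", cleavage, available embryos and "Number of high-quality embryos". The Abstract gives the purpose as to "evaluate the effect of acupuncture on increasing the number of retrieved oocytes after controlled ovarian hyperstimulation in women with POR".

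Under Statistical analysis, "All analyses will be based on the intention-to-treat principle" and "Missing data will be imputed using the multiple imputation method". The tests are an "independent *t*-test or Wilcoxon rank-sum test for continuous variables, and a chi-square test or Fisher exact test for categorical variables".

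Two other places bear on how often a denominator could be zero. The inclusion criteria require a previous conventional cycle with at most three oocytes, and the Background names frequent cycle cancellation as a feature of POR without giving a figure.

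**The concern.** A rate built from these counts is conditional on something that happens after randomization. The first count in the chain is the primary outcome, so if acupuncture works as hoped, it also changes who has a rate and how many oocytes the rate is based on. The women compared are then a subset whose make-up can differ by arm.

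For a woman with no oocytes the fertilization rate is not missing; there is no such quantity. The same holds for a woman with oocytes but none fertilized, for any rate taken over fertilized oocytes or embryos. The two rules in Statistical analysis do not cover this. Analyzing only women with a rate is not intention-to-treat, and multiple imputation recovers unobserved values rather than values that cannot exist.

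At stake is whether the four embryology comparisons keep the protection of randomization. The primary outcome is a count that can be zero, so it does not have this problem.

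**Working it through.** **1. Inputs.** From Sample size calculation: mean (SD) oocytes 4.88 (1.84) with acupuncture and 3.95 (1.66) in controls, 57 per group for 80% power at two-sided 5%, and 70 per group recruited. The protocol states no figure for the rates.

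**2. Check of the stated sample size.** Difference = 4.88 − 3.95 = 0.93. SD = √[(1.84² + 1.66²)/2] = 1.752. The normal formula gives n = 2 × (1.960 + 0.842)² × 1.752²/0.93² = 56 after rounding up. The t-distribution version gives 56.7, hence 57. The stated size reproduces, so these means and SDs can be carried forward.

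**3. Women with no oocytes, from those figures.**

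| | Normal, P(X < 0.5) | Poisson, exp(−mean) | Women of 70 |
|---|---|---|---|
| Control | Φ[(0.5 − 3.95)/1.66] = 1.9% | exp(−3.95) = 1.9% | about 1.3 |
| Acupuncture | Φ[(0.5 − 4.88)/1.84] = 0.9% | exp(−4.88) = 0.8% | about 0.6 |

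This makes no allowance for cancelled cycles.

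**4. Later denominators.** Assume Poisson oocyte counts and an independent 70% chance of fertilization per oocyte. Fertilized oocytes per woman then average 0.70 × 3.95 = 2.77 and 0.70 × 4.88 = 3.42. The share of women with none is exp(−2.765) = 6.3% in controls and exp(−3.416) = 3.3% with acupuncture, or about 4.4 and 2.3 of 70. Rates taken over fertilized oocytes would be undefined for these women.

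**5. Size of the selection effect.** Let c0 and c1 be the shares with no oocytes in control and acupuncture, cancellations included. Suppose women who gain a retrieval through treatment fertilize at 50% and all others at 70% (assumed). The mean rate among acupuncture women with oocytes is [(1 − c0) × 0.70 + (c0 − c1) × 0.50]/(1 − c1), against 0.70 in controls.

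| c0 vs c1 (assumed) | No rate, of 70 per arm | Acupuncture rate | Shift |
|---|---|---|---|
| 2% vs 1% | 1.4 vs 0.7 | 69.8% | −0.2 points |
| 10% vs 5% | 7 vs 3.5 | 68.9% | −1.1 points |
| 20% vs 10% | 14 vs 7 | 67.8% | −2.2 points |

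In each row no woman is worse off, and fertilized oocytes per randomized woman rise slightly. For example, with 3.95 oocytes per retrieval and one oocyte for each woman who gains a retrieval, the last row gives 0.80 × 3.95 × 0.70 = 2.21 against 2.21 + 0.10 × 1 × 0.50 = 2.26.

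**6. Only if oocytes were pooled across women.** Average oocytes per woman = (4.88 + 3.95)/2 ≈ 4.4. Design effect = 1 + (4.4 − 1) × ρ. True type I error of a plain chi-square test = 2 × [1 − Φ(1.96/√design effect)].

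| ρ (assumed) | Design effect | Type I error |
|---|---|---|
| 0.1 | 1.34 | 9.0% |
| 0.2 | 1.68 | 13.0% |
| 0.3 | 2.02 | 16.8% |

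Rates over fertilized oocytes or embryos have fewer units per woman, so the inflation would be smaller at the same ρ.

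**The case against.** **The denominators are inferred.** The article names the rates but does not define them, and a full protocol or analysis plan may do so. That stands: the missing definition is not the finding. Every usual choice (retrieved oocytes, fertilized oocytes, embryos) is counted after randomization and can be zero, so the conflict with the blanket intention-to-treat statement remains whichever is used.

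**Inflated type I error.** A reader might infer that the protocol plans chi-square tests on pooled oocytes. It does not say so. A rate per woman is continuous, and the listed *t*-test or Wilcoxon test would then apply, with one value per woman and no clustering. The 9%–17% is therefore a caution for one possible implementation and rests on an assumed correlation.

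**Wrong direction of benefit.** A reader might also infer that the rates can mislead on sign. With assumed rates of 70% and 65%, controls have 0.70 × 3.95 = 2.77 fertilized oocytes and acupuncture patients 0.65 × 4.88 = 3.17: the rate is 5 points lower, yet there are 0.41 more per woman. These figures are assumed, and both results are correct answers to different questions, yield per oocyte and total yield. At a constant rate the count largely repeats the primary result. This is a reason to keep the rates, not evidence that they are wrong.

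**Small effect, secondary outcomes, exploratory trial.** This stands and limits the severity.

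**Conclusion.** The point holds in limited form. Rates conditional on a treatment-affected count, undefined for some randomized women, cannot be the intention-to-treat comparisons that the protocol promises for all analyses, and multiple imputation does not repair this.

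On the protocol's own means and SDs, about 1–2% of women would have no oocytes, and the matching shift in the fertilization rate is about 0.2 points. Shifts of 1 to 2 points need no-oocyte shares of 10% to 20% in controls, which are assumed; the documents give no cancellation figure. More women lack a defined rate at the later stages if those rates are taken over fertilized oocytes or embryos. The primary outcome and the sample size are unaffected.

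The documents do not support saying that a false-positive rate above 5% is built into the plan, that the rates give the wrong sign, or that they should be removed. The change is worth making because it is cheap, but the trial's main conclusion does not depend on it.

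**What to change.** - Make the between-group intention-to-treat comparison on the numbers of fertilized oocytes, cleaved embryos, available embryos and high-quality embryos per randomized woman. The two-sample tests already listed for continuous variables can be used; no new model is needed.
- Score 0 where the cycle was cancelled or yielded none. Use multiple imputation only where the outcome is truly unknown, for example after withdrawal before COH; such women must not be scored 0.
- Keep the four rates as supportive results among women with a non-zero denominator. State the denominator, label the results as conditional, and do not impute rates for the other women.
- If rates are tested across pooled oocytes or embryos, use a method that allows for clustering within woman.

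The cost is a small amendment to the secondary outcomes of a registered trial that is already recruiting, plus a little more analysis. Table 1 already schedules every count, so there are no new data or visits and no change in sample size.

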### Statistical methods

#### Sample size calculation

There are no available clinical studies on the effect of acupuncture for POR. Based on results of a TEAS study on POR [18], we assumed the mean (SD) number of retrieved oocytes would be 4.88 (1.84) in the acupuncture group and 3.95 (1.66) in the control group. A sample size of 57 participants per group would be needed to provide 80% power and a two-sided significance level of 5%. Allowing for a 20% dropout rate, 140 participants will be recruited with 70 participants per group.

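### Six secondary outcomes have a scheduled baseline, but the only stated between-group comparison is an unadjusted test; adjusting for baseline would be at least as precise at no cost in data

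*Protocol article*

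**What the plan says.** Table 1 of the protocol article schedules AFC, AMH, basal FSH, LH and E2, and the SAS score at W0 and again at W12. The Outcome measures section agrees: "Ovarian reserve will be assessed at baseline and after acupuncture or nontreatment period", and "SAS will be assessed at baseline and after acupuncture or nontreatment period".

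The Statistical analysis section names one approach for all such variables: "Comparisons between groups will be analyzed using an independent *t*-test or Wilcoxon rank-sum test for continuous variables". No covariate, regression model or centre term is named, and the quantity to be tested (final value or change) is not stated.

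Three other places bear on the point:
- Randomization and masking: allocation is 1:1, in blocks stratified by centre. Study design lists nine hospitals.
- Sample size calculation: the trial is sized on the number of retrieved oocytes alone.
- Discussion: the planned conclusion covers retrieved oocytes and ovarian reserve.

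**The concern.** Each woman is due to have her own pre-treatment value on six outcomes, yet the stated tests have no place for a covariate. A test on final values leaves in the error term all the between-woman variation that the baseline could explain. A test on change uses the baseline, but with a fixed coefficient of 1, which over-corrects whenever the true slope is below 1. In both cases a chance baseline difference between arms passes into the estimate.

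Randomisation is stratified by centre only, so nothing in the design balances baseline AFC or AMH. No power is assured for these outcomes, because the trial was sized on oocyte number. How the collected data are analysed is therefore the one means left of sharpening the ovarian-reserve results without enrolling more women.

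**Working it through.** **The plan's own figure.** The inputs are "4.88 (1.84) in the acupuncture group and 3.95 (1.66) in the control group", 80% power and two-sided 5%, from Sample size calculation.
- Difference: 4.88 − 3.95 = 0.93. Pooled SD: √[(1.84² + 1.66²)/2] = 1.752.
- The normal approximation gives 56 per group. The exact noncentral-t calculation gives 57 (power 0.802 at 57, 0.795 at 56).
- The stated 57 per group is reproduced. The recruited 70 per group equals 56/0.8; 57/0.8 would round up to 72, so the total of 140 agrees within 3%. Nothing below alters this, because the primary outcome has no W0 measurement in Table 1.

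**Variance of the treatment effect.** Take n women per arm, the same SD σ at both times, and baseline-final correlation r (assumed; not in the document).
- t-test on final value: 2σ²/n, set to 1.
- t-test on change: relative variance 2(1 − r).
- ANCOVA on own baseline: relative variance 1 − r², apart from a small cost for estimating the slope.
- ANCOVA relative to change: (1 − r²)/[2(1 − r)] = (1 + r)/2.

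| r (assumed) | Final value | Change | ANCOVA | Removed vs final value | Removed vs change |
|---|---|---|---|---|---|
| 0.3 | 1 | 1.40 | 0.91 | 9% | 35% |
| 0.5 | 1 | 1.00 | 0.75 | 25% | 25% |
| 0.7 | 1 | 0.60 | 0.51 | 49% | 15% |

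A simulation (5,000 runs, 57 per arm) gave ANCOVA ratios of 0.916, 0.754 and 0.512, and change-score ratios of 1.376, 1.008 and 0.598, in line with the formulas.

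**In sample-size terms.** A final-value t-test with 57 per arm is matched by ANCOVA with 57 × 0.91 = 52, 57 × 0.75 = 43 and 57 × 0.51 = 30 per arm (rounded up).

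**In power terms, as an illustration only.** Borrow the primary outcome's standardised effect, 0.93/1.752 = 0.53, with 57 per arm (normal approximation). Final-value power is 0.809. Change-score power is 0.668, 0.809 and 0.955 at r = 0.3, 0.5 and 0.7. ANCOVA power is 0.844, 0.905 and 0.978. The document gives no effect size for any of the six outcomes.

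**Chance imbalance.** With 70 per arm, the baseline difference between arms has SD √(2/70) = 0.169 in units of σ. A 2-SD imbalance is 0.338σ, and about 5% of trials reach that, in either direction, for a given outcome.
- Final-value estimate shifts by r × 0.338σ: 0.10σ, 0.17σ and 0.24σ at r = 0.3, 0.5 and 0.7.
- Change-score estimate shifts the opposite way by (1 − r) × 0.338σ: 0.24σ, 0.17σ and 0.10σ.
- ANCOVA removes this linear part.

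**The case against.** Several stronger readings are tempting, and the document does not support them.

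- *The baseline is ignored.* A reader might infer this from the named tests. But the text does not fix the quantity tested, and a t-test or Wilcoxon test on change would use the baseline. What stands is that the quantity is left open and that neither choice is as efficient as adjustment.
- *The unadjusted result is biased.* It is not. Under randomisation the tests keep their type I error, and their standard error already allows for chance imbalance. Adjustment improves precision and corrects for the imbalance that happens to occur in this one trial.
- *A large share of the precision is lost.* This depends on an unknown correlation that may differ among the six outcomes. Low AFC or AMH is one route to eligibility, which narrows the baseline range for many women, and FSH, LH and E2 may be measured anywhere in cycle days 2 to 5. Low correlations are therefore plausible, and at 0.3 the gain over final values is only 9%. The formulas also describe the t-test and do not directly cover the Wilcoxon option.
- *A planned anxiety claim is at risk.* The planned conclusion in the Discussion covers oocytes and ovarian reserve. Relief of anxiety appears in the Background, as earlier evidence; SAS is simply a listed secondary outcome.
- *Centre adjustment would bring a known gain.* No between-centre variance is given, and own baseline may already absorb stable site differences. Centre still belongs in the model because it is the randomisation stratum.

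It is also fair to say that the trial calls itself exploratory, and that an article may leave modelling detail to a fuller document. However, the article does not stay silent here: it states a method, and that method takes no covariate. The direction of the comparison does not depend on r either. Apart from the small cost of estimating the slope, ANCOVA is at least as precise as both simple tests for every r from 0 to 1.

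**Conclusion.** The point holds as an efficiency weakness in six secondary outcomes. The stated tests are valid but less precise than baseline adjustment. At assumed correlations of 0.3 to 0.7, the avoidable variance is 9% to 49% if final values are tested and 35% to 15% if changes are tested. These figures assume equal SDs at the two times and a linear relation with the same correlation in both arms. The gain from a centre term cannot be quantified from the document. The change is worth making because it uses only data already scheduled and settles which quantity is analysed, but the trial's validity does not depend on it.

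**What to change.** Before unblinding, replace the two-group test for these outcomes with wording such as: *AFC, AMH, FSH, LH, E2 and SAS score will each be analysed by ANCOVA of the post-treatment value on treatment arm, the outcome's own baseline value and centre. Skewed hormone measures will be analysed on the log scale. Adjusted mean differences, or ratios for log-scale outcomes, will be reported with 95% confidence intervals.*

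The cost is analysis wording only, with no new visits, measurements or participants. Nine centres use 8 degrees of freedom. With 56 women per arm after 20% dropout, the model has 1 + 1 + 1 + 8 = 11 parameters, leaving 112 − 11 = 101 residual degrees of freedom.
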